## Methods

### Study design

RE-HOPE will be a sequential mixed methods design study comprising two phases.

In the qualitative phase, we will conduct a study within the interpretive paradigm using a phenomenological design. Focus groups with stakeholders will be conducted using a semi-structured interview guide developed by the research team. Meetings will be held at participants' workplaces, and each session will be audio-recorded, transcribed verbatim, validated, and coded. Eligible professionals will be contacted by telephone and invited to participate voluntarily. Barriers to hypertension control identified during the formative phase, including difficulties in patient identification and challenges in coordination among health system actors affecting the delivery of cardiovascular risk programs, will be incorporated into the intervention design. Accordingly, the intervention seeks to reduce gaps in screening, improve awareness of hypertension, and strengthen healthcare professionals' knowledge of the diagnosis, treatment, and control of hypertension.

The second phase will consist of a quantitative study aimed at assessing the effectiveness of the implemented strategy. A single-arm intervention design will be used to evaluate longitudinal changes in blood pressure through within-participant comparisons of baseline and follow-up measurements.

The RE-HOPE study will be conducted in primary healthcare centers in Santander, Colombia. This manuscript describes the intervention protocol and follow-up procedures implemented by the community health team.

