### Implementation general framework

The RE-HOPE study will be conducted within the general framework of the Exploration, Preparation, Implementation, and Sustainment (EPIS) model, which will guide the implementation process and inform the assessment of determinants influencing implementation. The EPIS model is a conceptual implementation framework that facilitates understanding of key contextual factors and their interactions throughout the implementation and sustainment phases. Specifically, EPIS comprises four stages: (1) exploration of the need for change; (2) preparation for intervention adoption; (3) intervention implementation; and (4) intervention sustainment over time (13). Across these four phases, the study will examine factors related to both the inner context (characteristics of healthcare institutions, providers, administrators, and staff) and the outer context (government agencies, communities, pharmacies outside clinics, and insurance companies/providers), as well as patient characteristics that may affect implementation. Table 1 presents the operationalization of the intervention components according to the EPIS framework, including contextual factors, implementation strategies, involved actors, implementation outcomes, and indicators. The RE-HOPE model will adapt a community-based intervention implemented by a working team comprising an operational coordinator, a data manager, community health workers (nursing assistants), community leaders, and healthcare professionals at primary care centers (PCCs). The roles of the team members are described in Table 2. The workload will be organized according to the identification and follow-up of individuals with hypertension in each community to which each nursing assistant is assigned (district or municipality). The individuals with hypertension may be served by one or more PCCs in each district or municipality.

**Table 1 T1:** Implementation of the RE-HOPE approach based on EPIS model.

EPIS phase	Context factor	Implementation strategy	Responsible actors	Implementation outcome	Indicator	Data source/time point
Exploration	Outer context	Engagement with community leaders and health authorities to introduce the RE-HOPE approach	Research team, community leaders, health authorities	Acceptability	Proportion of stakeholders reporting high acceptability of the intervention in the qualitative phase	Structured stakeholder survey; pre-implementation

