### Follow-up

CHWs will arrange appointments for home follow-up visits (months 1, 3, 6, 9, and 12), and blood pressure will be measured according to the standardized protocol. Additional data will be collected on anthropometric variables, physical activity habits, tobacco and alcohol use. The follow-up framework aligns with the guidelines of the International Society of Hypertension for hypertension management and the WHO guidelines (2, 15). Barriers to accessing antihypertensive medications and statins within the healthcare system will also be evaluated. If participants are found to have uncontrolled hypertension, they will be referred to their corresponding primary care center for medical evaluation and adjustment of antihypertensive therapy. In cases of critically elevated blood pressure (>180/100 mmHg), with or without signs of target organ damage, emergency care will be recommended.

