### Outcomes and measurements

The primary outcome is the change in systolic blood pressure levels from baseline to 12 months.

Secondary outcomes include:
−Systolic and diastolic blood pressure levels from baseline to 12 months.−Proportion of participants achieving systolic blood pressure control (<140 mmHg) from baseline to 12 months.−Changes in the prevalence of healthy behaviors (including reduced tobacco use and alcohol consumption, and regular physical activity).−Proportion of non-institutionalized individuals with hypertension (i.e., those not enrolled in cardiovascular risk management programs).−Change in cardiovascular risk score using the WHO risk prediction tools (16).−Identification of barriers and facilitators related to cardiovascular risk management.−Change in CHWs' cognitive and attitudinal competencies, assessed through knowledge, attitudes, and practices questionnaires administered to primary care health personnel.

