### Sample size

Based on the findings of a meta-analysis by Mills et al. (8), the primary efficacy outcome sample size calculation assumed a 7-mmHg reduction in SBP (SD 50) after 12 months of follow-up, and a correlation of 0.3 between baseline and follow-up measurements. Using 90% statistical power and a two-sided significance level of 5%, the required initial sample size was estimated at 1,912 participants, increasing to a final sample size of 2,294 after allowing for approximately 20% lost, with participants recruited proportionally across provinces.

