#### Clinical effectiveness outcomes

Descriptive analyses will summarize continuous variables using means or medians, along with standard deviations or interquartile ranges, depending on the distribution of the data. Absolute and relative frequencies represent categorical variables. For the primary and secondary outcomes, the analysis will produce estimates using linear mixed models of the continuous outcomes (change in systolic blood pressure, systolic and diastolic blood pressure), and generalized linear mixed models for the categorical outcomes (proportion of hypertension control, proportion of modification of life styles, proportion of participants in low, moderate, high and extremely high cardiovascular risk), estimating mean and 95% confidence intervals at baseline and 3, 6, 9, and 12 months of follow-up. The models will include random intercepts accounting for within-subject correlation over time, and the fixed effects will include sex, region, age and anthropometric measures. We will impute missing covariate data using the predictive mean matching algorithm implemented in the mice package (version 3.16) in R statistical software (version 4.3). We will not impute missing outcome because these are expected to be approximately missing at random, primarily due to participants moving out of their municipality of residence. Accordingly, the mixed-effects model will be fitted using the observed data. Finally, we will perform a sensitivity analysis comparing the primary and secondary outcomes between participants who are aware of their condition and receiving treatment and those who are unaware of their condition. The mixed-effects models will be fitted using the lme4 (version 1.1-35.1) and mgcv (version 1.9-1) packages in R.

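### The stated primary model makes no allowance for SBP change varying between community health workers or care centers; if it does vary, the 95% CI for the 12-month change will be too narrow

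*Protocol article*

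**What the plan says.** All references are to the protocol article.

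- **Design and outcome.** Under Study design: "A single-arm intervention design will be used to evaluate longitudinal changes in blood pressure through within-participant comparisons of baseline and follow-up measurements". Under Outcomes and measurements: "The primary outcome is the change in systolic blood pressure levels from baseline to 12 months".
- **Model.** Under Clinical effectiveness outcomes, linear mixed models are planned for continuous outcomes and generalized linear mixed models for categorical ones. "The models will include random intercepts accounting for within-subject correlation over time"; the fixed effects are sex, region, age and anthropometry. The section also fixes the handling of missing data and the software packages. It mentions no CHW, center or municipality effect, no cluster-by-visit term and no robust standard error.
- **Delivery.** Implementation general framework organizes the workload by the hypertensive individuals found "in each community to which each nursing assistant is assigned (district or municipality"), and adds: "The individuals with hypertension may be served by one or more PCCs in each district or municipality". Table 2 gives the nursing assistants (the CHWs) both the counseling and the blood pressure measurement, and gives prescribing to the health workers at the centers.
- **Sample size.** The calculation "assumed a 7-mmHg reduction in SBP (SD 50) after 12 months of follow-up" and a baseline-to-follow-up correlation of 0.3. No ICC or design effect is stated.

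**The concern.** Participants in one area share counselors, blood pressure assessors and prescribers. The article itself expects delivery to differ: Table 1 tracks visits, workload and supervision per CHW, and the implementation framework examines center and provider characteristics. Such differences could plausibly alter how far SBP falls, and not just where it starts.

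The region term does not deal with this. With SBP level as the response, a region main effect only shifts the level. With change as the response, it absorbs differences between regions but not those between CHWs or centers within a region.

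In a single-arm study, the interval around the mean change is the main quantitative result. The Discussion intends it to inform scaling to other regions, that is, to other CHWs and other centers. An interval that treats participants as independent leaves out that source of uncertainty.

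**Working it through.** **The plan's own figures.** The article gives no standard error or interval to reproduce. Its final sample of 2,294 is 1,912 × 1.2 = 2,294.4. With 20% lost, 2,294 × 0.8 = 1,835 are evaluable. The SD of change implied by the stated inputs is 50 × √(2 × (1 − 0.3)) = 59.16 mmHg. The paired formula with these inputs gives 751, not 1,912; that is a separate matter and nothing below depends on it.

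**Which cluster effects matter.** Write SBP for a participant of CHW *k* at visit *t* as visit mean + *a*ₖ + *d*ₖₜ + participant effect + error. In month 12 minus baseline, *a*ₖ cancels; *d*ₖ,₁₂ − *d*ₖ,₀ does not. A simulation of a balanced random-intercept model (30 CHWs × 64 participants, 2,000 runs, nominal 95%) bears this out:

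| Cluster effect | Coverage |
|---|---|
| None | 94% |
| CHW intercept only, SD 10 mmHg | 95% |
| CHW variation in change, ICC 0.01 | 87% |
| CHW variation in change, ICC 0.02 | 81% |
| CHW variation in change, ICC 0.05 | 64% |

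**Size.** Assumptions not in the documents: 20 to 40 CHWs, equal cluster sizes, ICC of change 0.01 to 0.05. Design effect DE = 1 + (m − 1) × ICC, with m = 1,835/20 = 91.75 or 1,835/40 = 45.9. The true SE divided by the model SE is √DE, and coverage is 2Φ(1.96/√DE) − 1. Half-width is 1.96 × 59.16 × √(DE/1,835), which is 2.71 mmHg when DE = 1.

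| CHWs | ICC | DE | True SE / model SE | Coverage | Correct half-width (mmHg) |
|---|---|---|---|---|---|
| 40 | 0.01 | 1.45 | 1.20 | 90% | 3.26 |
| 40 | 0.05 | 3.24 | 1.80 | 72% | 4.88 |
| 20 | 0.01 | 1.91 | 1.38 | 84% | 3.74 |
| 20 | 0.05 | 5.54 | 2.35 | 60% | 6.37 |

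The ratios and coverages depend only on the number of clusters and the ICC; the half-widths also depend on the plan's SD of 50.

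**Covariance over visits.** A random intercept gives the contrast an SD of √(2 × (mean variance − mean covariance)). For illustration, assume a baseline SD of 12, a follow-up SD of 18, a baseline-to-follow-up correlation of 0.3, and visits at 0, 3, 6, 9 and 12 months. Mean variance is (144 + 4 × 324)/5 = 288. The true SD of the contrast is √(144 + 324 − 2 × 64.8) = 18.4.

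- Correlation among follow-up visits 0.30: mean covariance (4 × 64.8 + 6 × 97.2)/10 = 84.2; model SD √(2 × 203.8) = 20.2, so the model SE is about 10% too large.
- Correlation among follow-up visits 0.65: mean covariance (4 × 64.8 + 6 × 210.6)/10 = 152.3; model SD √(2 × 135.7) = 16.5, so the model SE is about 10% too small.

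The same visit SDs give opposite errors, depending on a correlation that the article does not state.

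**The case against.** The strongest reply is that the harm is conditional. The comparison is within participants, so stable differences between CHWs or centers drop out, and the article gives no cluster counts or ICC. The 60% coverage is the worst corner of an assumed grid. All of that stands, and the point is worded accordingly.

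It can also be said that an article condenses the plan and never says that participant intercepts are the only random effects. That carries less weight here, because the section goes as far as random effects, fixed effects, imputation method and package versions. An analyst following it would fit no cluster term. The exact covariance structure and small-sample correction could be left to an analysis plan; the level at which the intervention is delivered should not be lost.

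Several stronger readings are tempting but not supported:

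- *Unequal variance over visits will narrow the interval.* The direction is not fixed, as shown above.
- *Baseline SBP is truncated at 140 mmHg.* Only partly: criterion (c) under Population and sample admits known hypertensive individuals not regularly attending a program, with no blood pressure threshold.
- *There is one CHW per community.* The text says that each nursing assistant is assigned to a community, not that each community has only one.
- *Modeling change conflicts with estimating a baseline mean.* SBP level is also listed as a modeled outcome, so a baseline mean has a place.
- *Month 1 data are discarded.* Follow-up says "CHWs will arrange appointments for home follow-up visits (months 1, 3, 6, 9, and 12"), while the analysis section plans on "estimating mean and 95% confidence intervals at baseline and 3, 6, 9, and 12 months of follow-up". That list covers the visits at which means are estimated; it does not exclude month 1 from the fit. It is a wording mismatch with no bearing on clustering.

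**Conclusion.** The concern holds in conditional form. The stated primary model accounts for correlation within participants only, while counseling, measurement and prescribing are organized by area. If the 12-month SBP change varies between CHWs or centers, the 95% interval is too narrow. Under the assumed 20 to 40 CHWs, 1,835 evaluable participants and ICC of change of 0.01 to 0.05, the true SE is about 1.2 to 2.4 times the model SE and coverage runs from about 90% down to 60%. The actual size cannot be known from the article. Because clusters would be large, even an ICC of 0.01 matters. The random intercept's equal-variance, equal-correlation assumption is a secondary weakness of unknown direction.

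A reader might infer that the interval is certain to be too narrow. The documents do not support that: with purely additive cluster effects, coverage stays near 95%. The estimate of mean change is not in question here, only its stated precision.

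**What to change.** - Record CHW ID and center ID for every participant.
- Report the month 12 minus baseline SBP contrast with cluster-robust standard errors at CHW or community level, using a small-sample correction such as CR2.
- Alternatively, include a CHW or center random effect on the change. In a model of SBP level, that means a random visit effect per CHW or center; a random intercept alone would not help. If change itself is the response, a cluster intercept is enough.
- Apply the same clustering to the binary outcomes.
- Preferably, replace the random intercept with an unstructured within-participant covariance and visit as a categorical effect. This is sound whichever way the equal-variance error would have run.

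The cost is a sentence or two in the analysis plan, two ID variables, somewhat more analysis work and wider intervals. Recruitment, visits and care do not change.

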
The “Implementation, Integration, and Institutionalization of a Community-Based Care Program to Reduce Cardiovascular Risk in Santander” (RE-HOPE) study will be developed to optimize community-level hypertension management by integrating CHWs into the processes of early detection, follow-up, and blood pressure control. The RE-HOPE model combines detection and referral mechanisms, structured health counseling, ongoing monitoring, and the use of simplified clinical algorithms to facilitate therapeutic decision-making and improve clinical outcomes.

Currently, cardiovascular risk programs at both the regional and national levels have gaps that limit their coverage. First, a high proportion of individuals with hypertension are unaware of their condition and therefore do not access cardiovascular risk programs; on the other hand, although some individuals with hypertension are aware of their disease, participation in institutional activities remains suboptimal. It is estimated that compliance with institutional programs is only around 60% (11). Additionally, among those already enrolled in cardiovascular risk programs, it is necessary to overcome some of the barriers identified by users in order to achieve hypertension control, including access to health services, coverage, education about the disease, and interaction with patients (12). The RE-HOPE model is designed to address these gaps by helping institutional cardiovascular risk programs increase their coverage. This will be achieved by strengthening patient engagement, reinforcing home-based health education, and improving continuity of care through more patient-centered strategies.

The distinguishing feature of the RE-HOPE study is the timely institutionalization of patients into cardiovascular risk management programs through structured coordination between community case detection and primary healthcare providers. We aim to develop an innovative and potentially scalable strategy that, if proven effective, may help close existing gaps in hypertension control in LMICs such as Colombia.

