### Data collection

CHWs will collect baseline data, health counseling activities, and follow-up visit information using digitized forms via the REDCap® system. Data collected will include:
-Sociodemographic variables: age, sex, and health insurance affiliation.-Lifestyle behaviors: tobacco/vape use, alcohol consumption, and weekly physical activity.-Clinical measures: systolic and diastolic blood pressure.-Anthropometric measurements: weight, height, body mass index (BMI), waist circumference, hip circumference, and waist-to-hip ratio.-Cardiovascular risk scores: calculated using WHO tools.-Laboratory results will be obtained from the clinical laboratories of the assigned primary care providers, as recorded in individual service provision records.

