### Secondary outcomes

After 12 months, the intervention will be assessed for its impact on blood pressure control (systolic blood pressure <140 mmHg) with a target of control around 60% of participants and the adoption of healthy behaviors, including increased physical activity and reduced tobacco and alcohol use compared to baseline. Improvements in participants' understanding of hypertension, its treatment, and the importance of regular medical follow-up may be observed. Additionally, the strategy will be evaluated for its potential to reduce the incidence of fatal and non-fatal myocardial infarction and stroke. The implementation of CHWs may contribute to improve participants' perceptions of support, trust, and accessibility to primary healthcare.

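### The missing-at-random assumption rests mainly on relocation, although the plan's own procedures make loss through disengagement foreseeable; the 12-month SBP fall and control proportion may be overstated, and no stated analysis checks this

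*Protocol article*

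**What the plan says.** Under Clinical effectiveness outcomes, the protocol article says that missing covariates will be imputed and missing outcomes will not, because the latter are "expected to be approximately missing at random, primarily due to participants moving out of their municipality of residence". Linear and generalized linear mixed models with random intercepts are then fitted to the observed outcomes. The listed fixed effects are sex, region, age and anthropometric measures. One sensitivity analysis is named: a comparison of participants who are aware of their hypertension and treated with those who are unaware of it.

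Other sections bear on how outcomes come to be missing:

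- **Population and sample**, criterion (c), admits people with known hypertension who do not attend programmes regularly.
- **Intervention**, first component, places invitation, consent and baseline data collection at the screening stage.
- **Intervention**, referral component, comes next. Non-attenders are followed up to find barriers, those who do not agree to attend are excluded, and home visits are scheduled once a person is enrolled in a programme. (The text says assist; in context it appears to mean attend.)
- **Follow-up** has blood pressure measured at those home visits, at months 1, 3, 6, 9 and 12.
- **Study design**: "A single-arm intervention design will be used to evaluate longitudinal changes in blood pressure through within-participant comparisons".
- **Sample size** plans the final number "after allowing for approximately 20% lost".
- **Expected results, Secondary outcomes** describes blood pressure control "with a target of control around 60% of participants".

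**The concern.** Relocation is a convenient reason for loss, because moving house need not have much to do with blood pressure. Declining to attend a clinic, or never being enrolled in a programme, is different. Someone who takes that route may receive neither the counselling nor the home measurement, and may be less likely to be treated. Their unobserved 12-month SBP could well be higher than their earlier readings, sex, region, age and body measurements predict. In that case missing at random fails for them.

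The listed model terms contain no attendance, enrolment or adherence variable that could absorb this. The one named sensitivity analysis compares two kinds of participant and does not vary the missing-data assumption. With no second arm, selective loss passes straight into the headline change and the control proportion.

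**Working it through.** **Planned loss.** The allowance reproduces as 1,912 × 1.2 = 2,294.4, against 2,294 in the article. That corresponds to a loss of 1 − 1,912/2,294 = 16.7%; a loss of exactly 20% would need 1,912/0.8 = 2,390. The illustration uses the article's nominal 20%, with 16.7% as a check.

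**Inputs.** The article "assumed a 7-mmHg reduction in SBP (SD 50) after 12 months of follow-up", with "a correlation of 0.3 between baseline and follow-up measurements", and expects about 60% control. It gives no outcomes for lost participants, so those below are assumptions.

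**True mean fall among all participants.** Formula: (1 − d) × fall in stayers + d × fall in the lost, with d = 0.20 and stayers falling 7 mmHg.

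| Assumed fall in the lost (mmHg) | Mean fall in all (mmHg) |
|---|---|
| 7 | 0.8 × 7 + 0.2 × 7 = 7.0 |
| 3.5 | 0.8 × 7 + 0.2 × 3.5 = 6.3 |
| 0 | 0.8 × 7 + 0.2 × 0 = 5.6 |
| −3.5 (a rise) | 0.8 × 7 − 0.2 × 3.5 = 4.9 |

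At 16.7% loss the zero-fall row is 0.833 × 7 = 5.8 mmHg.

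**What the planned type of model would report.** A random-intercept model with visit effects was simulated at baseline and months 1, 3, 6, 9 and 12, with N = 2,294, SD 50, within-person correlation 0.3 and 300 runs. The variance ratio was treated as known and covariates were omitted. Stayers reached 40%, 70%, 85%, 95% and 100% of the 7 mmHg fall at the five follow-up visits.

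| Loss mechanism | Truth | Mixed model | Completers only |
|---|---|---|---|
| Unrelated to SBP, 20% | 7.0 | 6.9 | 6.9 |
| Driven by observed SBP (MAR), 24% | 7.0 | 7.0 | 5.2 |
| Disengaged, no fall, leave at varying visits, 20% | 5.6 | 6.6 | 6.9 |
| Disengaged, no fall, leave straight after baseline, 20% | 5.6 | 7.0 | 6.9 |

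Monte Carlo error is about √(2 × 50² × 0.7/1,835)/√300 = 0.08 mmHg, where 1,835 = 0.8 × 2,294. As a check without simulation noise, the expected group means were put into the same generalised least squares estimator, with weight 0.80 on stayers and 0.04 on each of the five exit points. This gives 6.7 for the third row and exactly 7.0 for the fourth. The overstatement in these scenarios is therefore about 1.0 mmHg (6.6 − 5.6) to 1.4 mmHg (7.0 − 5.6).

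The last row is closest to the exclusion in the referral component, because a person removed there has no follow-up reading.

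**Control proportion.** If 60% of those observed at month 12 are controlled and 20% are lost, control among all enrolled is 0.8 × 60% = 48% if none of the lost are controlled, and 48% + 20% = 68% if all are. Intermediate assumptions of 20%, 30% and 40% control among the lost give 52%, 54% and 56%.

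**Bias or power?** Taking the SD of 50 and correlation of 0.3 at face value, 1,912 pairs give a standard error of √(2 × 50² × 0.7/1,912) = 1.35 mmHg. Power at a fall of 5.6 mmHg is then about 98%. The issue is bias, which a large sample does not remove.

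**The case against.** The strongest reply is that a mixed model on observed data is a sound primary analysis. It does not discard lost participants: anyone with a baseline or interim reading contributes. The second simulated row shows the benefit, with the model recovering 7.0 where completers alone give 5.2. This stands, and it rules out reading the plan as a completer analysis.

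Other limits also stand:

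- A reader might infer that the article shows disengagement to be a main route out. It does not. No section ranks reasons for loss, and the wording about relocation allows for others. The compliance of around 60% in the Introduction is background on institutional programmes, not a retention estimate for this study.
- A missed clinic appointment is not in itself a missing outcome, since blood pressure is measured at home. Non-attenders are to be followed up and reminders given. Refusing a home visit is not shown to mean stopping medication.
- The direction of bias is plausible, not established. The 48% to 68% range runs both ways, and no fall at all among the lost is a pessimistic assumption: many enter on a raised reading, so some regression to the mean is likely.
- A reader might infer that primary care records already supply blood pressure. Under Data collection, the phrase "as recorded in individual service provision records" refers to laboratory results only.
- The 60% control figure appears under Expected results and is not a decision rule.

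It can also be said that missing-data sensitivity analyses are often left to a statistical analysis plan. That would settle the matter had the article been silent. It states the assumption, its main reason and one sensitivity analysis, and that reason sits badly with its own eligibility and referral rules.

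**Conclusion.** The point holds in a limited form. The choice of model is sound. The weakness is that missing at random is supported mainly by relocation, while the article's own procedures make loss tied to engagement foreseeable and no stated analysis examines that possibility. Read in order, the referral exclusion falls after consent and baseline data; the text does not say whether it removes people from the analysis set or only from the intervention, and this needs to be settled.

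The 12-month fall may be overstated by about 1.0 to 1.4 mmHg against an expected 7. That size rests on three assumptions: 20% loss, all of it through disengagement, and no SBP fall among the lost. With a partial fall, or with some losses through relocation, it would be smaller. If loss does not depend on unobserved SBP, there is no material bias. A statement that the results will simply reflect those who stayed goes further than the documents allow.

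**What to change.** 1. Do not rest missing at random on relocation alone. Acknowledge loss through disengagement, and record the reason for each loss in the study database (for example moved, declined visits, left or never joined a programme, died).
2. Keep consented participants with baseline data who decline referral or counselling in the analysis set, and still seek their 12-month blood pressure. Reword the referral exclusion so that it is clear what a person is excluded from.
3. Keep the missing-at-random mixed model as primary. Add a sensitivity analysis in which disengagement losses are delta-adjusted or returned to baseline, with movers left under missing at random.
4. Report control with all enrolled as denominator and missing counted as not controlled, beside the model estimate. Label it a conservative supporting bound and do not make it the sole basis for judging the 60% expectation.

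The cost is some wording, one database field, the effort of seeking a final reading from people who have disengaged, and a few supporting analyses. The supporting figures may be less favourable than the primary ones.
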